## Abstract

**Abstract:**

**Background:**

The prevalence of women with primary dysmenorrhoea is high and negatively impacts physical and mental health. The intense cyclic episodes of pain generate central nervous system dysfunctional processing. In this sense, strategies focused on the central nervous system are important to re-establish normal functioning. Home-based self-administered transcranial direct current stimulation (tDCS) emerges as a strategy to modulate dysfunctional brain areas and improve the symptoms. This protocol aims to evaluate the effects of home-based self-administered tDCS for pain, premenstrual symptoms, physical performance, quality of life, electroencephalography and patient global impression in women affected by primary dysmenorrhoea.

**Methods and analysis:**

This is a single-centre, parallel, randomised, double-blinded clinical trial protocol. 40 women affected by primary dysmenorrhoea will be randomised into two groups (active-tDCS or sham-tDCS). Then, 20 consecutive sessions of home-based self-administered tDCS will be performed. The assessments will occur at five time points: baseline, after the 20th sessions, at the first, second and third cycles after tDCS interventions (follow-ups). Primary outcome will be pain according to visual analogue scale. Quality of life, premenstrual symptoms screening, depression, anxiety, physical performance, electroencephalography and participants’ satisfaction will be the secondary outcomes. A mixed analysis of variance will calculate the effect of stimulation.

**Ethics and dissemination:**

The study was approved by the ethics committee of the Federal University of Rio Grande do Norte (No. 6.037.756) and registered in the Brazilian Clinical Trials Registry (n° RBR-747k8vb). Participants may withdraw at any time without penalty. Free support will be available from the lead researcher if needed. All procedures will follow Good Clinical Practice and international ethical standards.

**Trail registration:**

https://ensaiosclinicos.gov.br/rg/RBR-747k8vb

STRENGTHS AND LIMITATIONS OF THIS STUDYParticipants will independently operate the transcranial direct current stimulation (tDCS) device through a smartphone application.The intervention involves a long-term treatment protocol consisting of 20 consecutive tDCS sessions.Long-term outcomes will be assessed across five menstrual cycles.Findings may have limited generalisability beyond the studied population and regional context.

## Introduction

 Primary dysmenorrhoea is defined as painful menstrual cramps generated in the uterus,^1^ characterised by the absence of visible structural abnormality or any pelvic gynaecological disease.^2^ Despite primary dysmenorrhoea being one of the most common gynaecological conditions among women, especially adolescents, it is frequently undertreated.^1^ Affecting approximately 25% of adult women and up to 90% of adolescent women, primary dysmenorrhoea is associated with the prevalence of severe and disabling pain.^3^ The incapacitating symptoms reported by women range from 15% to 20%.^3^ Painful symptoms in the lower abdomen and lumbar region are often accompanied by nausea, vomiting, dizziness, headache, fatigue and diarrhoea.^3^ The pain onset usually exhibits a predictable temporal pattern, starting right before or at the beginning of menstruation, lasting approximately 8–72 hours. Moreover, the pain is more severe during the first or second day of menstruation.^3 4^ The presence of signs and symptoms impacts women’s schooling, professional and leisure activities and consequently their quality of life.^4^

Some evidence shows that women affected by primary dysmenorrhoea present systemic pain’s dysfunctional processing, due to intense and cyclic episodes of pain.^5 6^ Peripheral nociceptive signals generated by receptor organs during the menstrual period are amplified, causing an increase in neuronal excitability due to peripheral sensory pain stimuli.^5 6^ In fact, the presence of central alterations may be part of the primary dysmenorrhoea pathophysiology, which is now considered a central sensitivity syndrome, similar to other chronic conditions, such as fibromyalgia and tension headaches.^3 7^ While the increased sensitivity of pain receptors after trauma or infection usually returns to normal over time, in chronic pain, hypersensitivity is sustained and amplified by an extensive central neural network that includes the dorsal spinal horn, the limbic system and cortical structures.^8^ The limbic and sensory systems mediate the hypervigilance cycle for sensory stimuli from pelvic organs, leading to chronic pain.^8^

In this context, specific techniques that can modulate central nervous system activity may be useful for pelvic pain control, such as primary dysmenorrhoea.^3^ Women with primary dysmenorrhoea reveal significant alterations in the functional connectivity of the anterior cingulate cortex and disruptions in brain metabolism and pain modulatory systems.^3 5^ Additionally, brain regions closely linked to cognitive and emotional pain processing, such as the medial prefrontal cortex, posterior cingulate cortex and insula, exhibit anomalous functional and structural changes in otherwise healthy women experiencing primary dysmenorrhoea.^3^ It is feasible that women affected by primary dysmenorrhoea manifest altered cross-network connectivity and a disbalance between these systems.^3^

Transcranial direct current stimulation (tDCS) is a non-invasive neuromodulation technique that releases an electrical microcurrent applied through the scalp, inducing changes in cortical excitability, according to the stimulation parameters.^9 10^ tDCS is considered a neuromodulatory intervention that induces alterations in the excitability of the human cortex, promoting physiological effects that extend to physical and behavioural aspects.^11 12^ Home-based remote tDCS solutions were widespread and advocated during the social isolation imposed by the COVID-19 pandemic period, yet, it appears to be following a clinical trend.^13^ Requiring participants to attend research sites, hospital facilities or rehabilitation clinics for multiple treatment sessions is a logistically challenging process. For many patients, these factors may lead to increased expenses for transportation, travel time, food and missed work or school, ultimately reducing access to treatment.

Home-based self-administered tDCS is a safe and easy-to-use treatment strategy with low adverse effects that could be an easier strategy to adhere to and implement. Also, home-based self-administered tDCS might be another treatment option for the many women affected by primary dysmenorrhoea. To date, several remote supervision tDCS protocols have been performed, focusing on chronic pain, musculoskeletal and behavioural disorders.^14^,^16^

We hypothesise that tDCS targeting the dorsolateral prefrontal cortex (DLPFC) and primary motor cortex (M1) will enhance therapeutic outcomes.^17 18^ Targeting the left DLPFC and the M1 with tDCS may be effective for primary dysmenorrhoea due to their roles in pain modulation and affective processing.^17^,^19^ The left DLPFC is a key node in the cognitive-affective dimension of pain and is involved in top-down pain control, emotional regulation and the processing of pain-related distress, which are commonly altered in women with dysmenorrhoea.^17^ Meanwhile, M1 stimulation has been shown to activate descending inhibitory pain pathways and reduce the perception of pain by modulating thalamocortical circuits.^10^ Combined stimulation of these areas may enhance both affective and sensory pain control, providing a dual mechanism of action that is particularly relevant for the multifaceted nature of menstrual pain. These brain regions are key components of the pain neuromatrix and are frequently characterised by hyperactivation and dysregulation in individuals experiencing chronic pain.^20^ Previous studies reported beneficial effects of tDCS on anxiety, functional capacity and pain in women with primary dysmenorrhoea.^17^,^19^ The stimulation of the DLPFC and M1 constitutes an optimal neuromodulatory strategy for addressing the multidimensional symptomatology of primary dysmenorrhoea, including both nociceptive and affective components.^17^,^19^

Considering these assumptions, this study aims to evaluate the effects of 20 home-based self-administered tDCS sessions in women affected by primary dysmenorrhoea over pain, quality of life, premenstrual symptoms, depression, anxiety, physical performance, electroencephalography and participants’ satisfaction.

## Methods

### Study design

This is a protocol study of single-centre, double-blind, parallel, sham-controlled, randomised clinical trial. The study protocol adhered to the Guidelines for Standard Protocol Items: recommendations for Interventional Trials. The study starts in April 2024 and is expected to be completed in April 2026. The participants will be followed for 6 months.

### Recruitment and eligibility criteria

The recruitment will be voluntarily recruited through social media (Facebook and Instagram) and posters placed in different departments of the university. Prospective participants will receive detailed information regarding the study methodology, encompassing its objectives, allocation to either sham or active groups, assessment protocols and intervention timeline.

The study is currently in the recruitment phase, which began in April 2024, and is expected to continue through April 2026, following the established inclusion criteria: (1) diagnosis of primary dysmenorrhoea, defined according to the No. 345 Primary Dysmenorrhoea Consensus Guideline^1^; (2) aged 18–45 years; (3) regular menstrual cycle lasting 28 to 32 days; (4) report a pain score of ≥4 on the numeric rating scale (0–10); (5) not lactating; (6) no history of brain surgery, tumour or intracranial metal implantation; no presence of metal implants in the head (7); and (8) no history of chronic genitourinary infections, alcohol or drug abuse. Exclusion criteria include (1) history of dizziness or epileptic disease, (2) current pregnancy, (3) severe headache after more than two tDCS sessions and (4) severe dizziness or migraine following more than two tDCS sessions.

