### Interventions

The entire treatment involves 20 consecutive sessions of home-based self-administered tDCS, one session per day. Initially, the participants will receive orientation about how to use the remote tDCS device. One physical therapist will instruct the participants about the tDCS protocol, download the application and demonstrate how to handle the device, including the position on the head, and operate it using the smartphone application. The Samphire App for IOS will be used. The training will also include the best practices for device preservation and conservation, such as leaving the tDCS in a safe place, and not over-exposing it to the sun or a heat source. Moreover, the researcher will inform the risks and guidelines related to potential expected adverse effects of use, which include redness at the site, itching where the electrodes are in contact with the skin, headaches after use, dizziness or nausea. The researcher will configure the smartphone application to be accessible in the participants’ native language (Brazilian Portuguese), with an option to switch to English. After training, participants will receive the device to use alone, according to instructions.

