### tDCS

The Samphire Neuroscience tDCS will be used. The device has four rectangular sponges (5.0 cm × 2.0 cm and 2.5 mm thickness) that must be impregnated by the user with a saline (0.9% NaCl) solution before placing the tDCS on the head. The two anode electrodes will be placed in the region of the M1 and the DLPFC of the left cerebral hemisphere, at points C3 and FC5, respectively. The two cathode electrodes will be placed under the same regions of the right hemisphere, C4 and FC6, according to the international electroencephalography (EEG) 10/20 system. Each participant will self-administer it during 20 sessions for 20 minutes per session. In the active tDCS group, the current will ramp up from 0 to 2.0 mA over 30 s, and ramp down over 30 s, for a 20 min total session time. In the sham tDCS group, to ensure blindness, the current will ramp up to 2.0 mA over 30 s, then ramp down to 0.01 mA, over 30 s. This method produces the same mimic sensations, such as itching and tingling observed during active tDCS, enabling blindness.^21^ Both active and sham tDCS groups will use identical tDCS devices and use the same App. The session type will be determined by a previous randomised code input into the Samphire App. During tDCS use, participants will receive instruction to feel free and continue with their habitual routine.

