### Sample size

The sample size will follow previous research conducted by our group. The numerical rating scale for pain is the primary outcome of assessing women affected by chronic pelvic pain. The participants also attended five sessions of tDCS using a C3/Fp2 assembly.^19^ G*Power (V. 3.1.9.4, Düsseldorf, Germany) estimated the power and sample size requirements through the use of the F-test from a repeated measures analysis of variance, including the main effects of group and time and the two-way interaction between group and time. Based on an alpha of 0.05 and power of 0.80, two groups (active group and sham group), sphericity of 1 and effect size of 0.25, a total of 34 participants will be required, with 17 participants randomised to each group. With anticipated attrition, we will add six more participants, totalling 40 participants (active group, n=20; sham group, n=20).

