### Randomisation, allocation concealment and blinding

A numerical sequence generated by appropriate software will assign each participant to the active tDCS group or the sham tDCS group, using a 1:1 allocation ratio. Each participant will be equally likely to belong to any group. An independent researcher not involved in the assessment or intervention will conduct all processes. Allocation concealment will be performed using opaque envelopes. Volunteers and researchers involved in assessments and interventions will maintain blinding to the participants’ allocation throughout the study.

Additionally, all procedures regarding the use of home-based self-administered tDCS will be performed for the sham group. First, the participants will position the device and turn it on. Then, they must follow the instructions and use the smartphone application. However, the tDCS will administer 2 mA of current with a ramp-up and ramp-down period of 30 s. Sham tDCS will involve administering active stimulation for a brief duration to replicate sensations (itching and tingling) observed during active tDCS.^21^

To initiate the tDCS protocol, participants will receive a code via email to access the smartphone application, allowing them to unlock 20 sessions of tDCS (one per day). The allocation of active or sham stimulation will be known only to a single researcher not involved in assessments or intervention.

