### Statistical analysis

SPSS software version 21.0 (IBM Corp., Armonk, NY, USA) will analyse the data. We will describe the clinical sociodemographic characteristics using mean and SD for continuous variables and frequency and percentage for dichotomous variables. Independent t-test and X^2^ will analyse continuous and categoric sociodemographic data, respectively. Intention-to-treat analysis will include the data from participants who do not complete the entire treatment protocol. We will define the significance level in all statistical testing as a p value less than 0.05. After data collection, we will identify the best distribution to represent the data according to the residuals Q–Q plot and histogram. The generalised estimated equations or mixed model will analyse the data (primary and secondary outcomes at baseline, after the fifth session, after the last session and follow-ups). We will also evaluate if it is necessary to insert fixed or random factors into the constant based on A/C, B/C and Q/C indices, X^2^/DF and the intraclass correlation coefficient. The link function will estimate the results according to the distribution of the dependent variable. Time, group (active and sham groups) and the interaction between them will represent the independent factors. The mean, mean difference, SD, 95% CI and p value for baseline, after the last session and follow-ups will illustrate the results. Cohen’ d will represent the effect size.

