### Harms

The researchers will carefully monitor adverse events in all steps of the study by asking patients, after each session of stimulation and during the follow-up periods, if they experienced any adverse events and the relationship of these events to treatment with tDCS. Any adverse event during the research period will be registered and considered for data analysis. The researchers will interrupt the sessions if any risk to the patients is suspected. To evaluate adverse effects, we will record any musculoskeletal symptoms, such as itching, tingling, burning sensation, headache, nausea and dizziness. Withdrawals will be excluded from the protocol and integrated as intention-to-treat analysis. Adherence to the number of missed sessions, number of dropouts and possible adverse events reported will be assessed.

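### Two exclusion criteria can be met only after randomised stimulation has begun, and the plan does not say clearly that the women they remove are still assessed

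*Protocol article*

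**What the plan says.** Under Recruitment and eligibility criteria the protocol article gives four exclusion criteria. The last two are "3) severe headache after more than two tDCS sessions and (4) severe dizziness or migraine following more than two tDCS sessions".

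On allocation, the tDCS section states: "The session type will be determined by a previous randomised code input into the Samphire App". The section on randomisation and blinding adds that "participants will receive a code via email to access the smartphone application, allowing them to unlock 20 sessions of tDCS (one per day"). No stimulation before allocation is described.

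On participants who stop, two sentences matter. Statistical analysis says: "Intention-to-treat analysis will include the data from participants who do not complete the entire treatment protocol". Harms says: "Withdrawals will be excluded from the protocol and integrated as intention-to-treat analysis".

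On timing, Outcomes and Participant timeline place T0 before any stimulation, T1 on the first day of menstruation after the 20 daily sessions, and T2 to T4 on the first day of the next three cycles.

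**The concern.** An eligibility criterion should be decidable before randomisation. One that can be met only after several randomised sessions is a post-randomisation exclusion. If it is applied as written, membership of the trial depends on how a woman reacts to her allocated treatment.

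At stake is the comparability of the arms on the primary outcome, VAS pain. If exclusion also ends follow-up, the missing T1-T4 values arise from a reaction to stimulation and may be related to both arm and pain. An intention-to-treat label cannot supply outcomes that were never collected. In a trial of 40, a few such losses concentrated in one arm would matter.

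**Working it through.** **1. Can the criteria be met before randomisation?** Both require more than two tDCS sessions, so at least three. The code that sets active or sham is in place before the first session, and the same access step unlocks all 20. With no run-in, the earliest moment either criterion can be met is after allocation. A reading as past experience with tDCS is conceivable, but criterion (1) is worded as a history while (3) and (4) are not, and nothing else supports that reading. So 2 of the 4 exclusion criteria act after randomisation.

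**2. Could the trigger differ by arm?** The Interventions section lists the expected adverse effects as "redness at the site, itching where the electrodes are in contact with the skin, headaches after use, dizziness or nausea". Headache and dizziness are on that list. Exposure differs greatly: active current is delivered over a 20-minute session, whereas in sham "the current will ramp up to 2.0 mA over 30 s, then ramp down to 0.01 mA, over 30 s". A difference in event rates is plausible. The article gives no rates by arm, so it is not shown.

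**3. What data would an excluded woman have?** Outcomes and Participant timeline give T0 before stimulation and T1 after session 20, with no pain visit between. (Figure 1 was not seen, so this rests on the text.) Statistical analysis mentions a time point after the fifth session, but neither visit section schedules one. A woman excluded during treatment and not seen at T1-T4 therefore has baseline pain only. The planned GEE or mixed model uses whatever values exist, but she contributes no post-treatment value, and neither method by itself repairs missingness that depends on unobserved pain.

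**4. The plan's own figure.** The sample size section states: "Based on an alpha of 0.05 and power of 0.80, two groups (active group and sham group), sphericity of 1 and effect size of 0.25", giving 34, raised to 40 for attrition. The number of measurements m and the correlation ρ are not given; I assume m = 2 and ρ = 0.5. For the within-between interaction:

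- λ = f²·N·m·ε/(1−ρ) = 0.0625 × 34 × 2 × 1 / 0.5 = 8.5
- df1 = (2−1)(2−1) = 1; df2 = (34−2)(2−1) = 32
- power = 0.807, so 34 is reproduced
- 6/40 = 0.15, and 34/(1−0.15) = 40, so the allowance is reproduced

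On the same assumptions power is 0.869 with 40 analysed, 0.830 with 36, 0.807 with 34 and 0.781 with 32. The six extra participants cover losses from all causes. The sample size is not in error on this ground.

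**5. Illustration of bias.** Suppose x of 20 active participants contribute no outcome, none are lost from sham, there is no true effect, and the lost women's mean pain is δ SD above the full arm mean. The mean of those remaining falls by x·δ/(20−x):

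| x lost | δ = 0.5 | δ = 1.0 |
|---|---|---|
| 0 | 0 | 0 |
| 1 | 0.5/19 = 0.026 | 1/19 = 0.053 |
| 2 | 1/18 = 0.056 | 2/18 = 0.111 |
| 3 | 1.5/17 = 0.088 | 3/17 = 0.176 |
| 4 | 2/16 = 0.125 | 4/16 = 0.250 |

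If sham also loses women and the lost differ from the retained by D SD in each arm, the shift is (p_active − p_sham)·D. With 20% against 5% that is 0.15 × 0.5 = 0.075 to 0.15 × 1.0 = 0.15 SD, and with equal proportions it is zero. Every value of x, δ, p and D here is assumed.

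**The case against.** The strongest reply is that the plan states intention-to-treat twice. The Harms sentence does not stop at exclusion: it goes on to integrate withdrawals as intention-to-treat. It can fairly be read as saying that stimulation ends and the woman is analysed as randomised, which agrees with Statistical analysis. That much stands. A reader might infer that the plan removes these women from the analysis, or that Harms contradicts Statistical analysis. The documents do not support either inference. The wording is ambiguous.

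A second reply is that no section says such women go unassessed, and that an article commonly leaves follow-up after discontinuation to the full protocol. This also stands as far as it goes: the harm is conditional on follow-up ending. But the point does not rest on missing detail. The article does address the matter, and does so by calling these events exclusion criteria and calling withdrawals excluded. That wording invites site staff to end follow-up.

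Third, a reader might infer that tolerability failures would be hidden. Harms says that adverse events, missed sessions and dropouts will be recorded and assessed, so that inference is not supported.

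Fourth, the direction of any bias is assumed. Nothing in the article links headache or dizziness after a session to menstrual pain at T1, and it describes home tDCS as having low adverse effects. This stands, and it is why the illustrated range starts at zero.

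**Conclusion.** On the plain reading, exclusion criteria (3) and (4) exclude randomised participants for events that include expected effects of the device. The withdrawal sentence leaves it unclear whether those women are still assessed. If they are not, they have no post-treatment pain value, and the loss may be related to treatment.

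The size of any resulting bias is unknown and may be zero. The range of 0 to 0.25 SD illustrates 0 to 4 active losses with pain 0.5 to 1.0 SD worse than the arm mean and no sham losses. It is not an estimate for this trial, and a reader should not take it as evidence that bias is present. The conclusion assumes that no run-in stimulation exists and that no pain visit falls between T0 and T1, as the text indicates.

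The wording should be corrected while recruitment is under way, because outcomes not collected cannot be recovered at analysis.

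**What to change.** Reconcile Recruitment and eligibility criteria, Statistical analysis and Harms in one short amendment:

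- Events that arise after randomisation should not stand as eligibility exclusions. The clinical content of (3) and (4), and any rule on stopping stimulation, remain with the investigators; no view is taken here.
- Replace the withdrawal sentence in Harms with a statement to this effect: every randomised participant, whether or not stimulation continues, is invited to the planned T1-T4 assessments and analysed in the allocated arm; data collection ends only if consent to follow-up is withdrawn.

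The T1-T4 visits are already planned, so the cost is the amendment and a small extra effort to keep contact with women who stop. Some will still decline follow-up, so the change reduces treatment-related missingness but does not abolish it.
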